## Abstract

**Background:**

Developing surgical skills among residents requires time and resources, often in conflict with the goals of efficiency and hospital economics in surgical practice. Optimizing resident training may prevent a decline in quality. Skilled surgeons are vital to effective and safe surgical performance, yet the training trajectory for surgical residents is often inefficient, particularly in the era of minimally invasive surgery. A framework that efficiently disseminates surgical skills is essential to cultivate skilled future surgeons within an acceptable time frame. Surgical telementoring (ST) aligns well with minimally invasive surgery because the mentee operating in the field shares the telementor’s perspective. Despite growing experience with telemedicine, data on educational outcomes remain limited.

**Objective:**

We aim to conduct a pilot randomized controlled trial (RCT). Data collection will inform a future full-scale RCT evaluating whether real-time ST, combined with structured postoperative coaching, is superior to traditional on-site mentoring in developing laparoscopic cholecystectomy skills among surgical residents.

**Methods:**

Eligible residents will be randomly assigned in a 1:1 ratio to either the intervention group (real-time ST and postoperative coaching) or the control group (traditional intraoperative hands-on teaching). This research adheres to the extended SPIRIT (Standard Protocol Items: Recommendations for Interventional Trials) statements for pilot RCTs and follows the intention-to-treat principle. Residents in both groups will perform 5 consecutive procedures under standardized intraoperative conditions. The primary outcomes are the Global Operative Assessment of Laparoscopic Skills (GOALS) score and the Non-Technical Skills for Surgeons (NOTSS). We hypothesize that the intervention group will show a 3- to 5-point improvement in the GOALS score compared with the control group. To achieve 0.8 statistical power, a *P* value <.05, and a 20% dropout rate in a definitive RCT, 12 residents per group are required. We present a pilot RCT with 5 residents per group. Challenges encountered during the trial will be reported, and amendments will be proposed to assess the need for a future definitive RCT.

**Results:**

The primary outcomes will be technical and nontechnical surgical skills, measured by the GOALS and NOTSS scores, respectively. Patient-reported experience measures and satisfaction scores of eligible mentees and mentors will be analyzed as secondary outcomes. The ST system configuration at the 2 inclusion centers was completed in December 2023. Ethics approval and the most recent update report to ClinicalTrials.gov were obtained on October 23, 2023, and December 8, 2024, respectively. Recruitment of residents to the study commenced in spring 2024. Recruitment is expected to be completed in May 2026, with data analysis in November 2026 and manuscript submission of results in January 2027.

**Conclusions:**

The SURGTEACH (Surgical Telementoring in Acquisition of Surgical Skills of Laparoscopic Cholecystectomy) trial is the first pilot RCT evaluating ST for educational outcomes. This research may provide high-quality evidence to improve surgical education, particularly in rural hospitals.

## Introduction

Developing surgical skills among residents is a time- and resource-consuming process [1]. Increasing demands for efficiency and hospital economics in surgical practice have contributed to a decrease in the number of surgeons per capita [2]. Concerning reports show increasingly limited access to the operating room (OR) during a surgical residents’ educational path [3]. Hence, efficient training trajectories for general surgeons are needed to ensure educational quality and efficiency [4].

Geographical challenges, including long distances and harsh weather conditions in Northern Norway, necessitate complex transportation arrangements to reach the hospital. A healthcare policy has been established that requires rurally located institutions to provide basic surgical care within an acceptable proximity to patients [5]. However, these institutions have limited access to surgical expertise, which may contribute to reduced quality of OR training for residents. The Norwegian National Medical Association has already taken this into account. This is one of the leading reasons for the reduced number of surgical procedures required to meet the Norwegian national requirements for achieving a specialty in general and colorectal surgery.

The centralization of surgical care, while improving outcomes for complex procedures at high-volume centers, has led to a decline in surgical services at smaller hospitals and greater challenges in recruiting and retaining consultant surgeons in rural areas.

This phenomenon is particularly pronounced in Scandinavian countries, where vast geographic distances amplify the impact of centralization policies. Norwegian rural hospitals increasingly rely on rotating surgeons and visiting consultants, creating discontinuity in surgical training programs and limiting residents’ exposure to consistent mentorship. A consequence of centralization is a lack of expert mentorship and a reduction in patient volume. Increased use of simulation training, surgical telementoring (ST), and information and communication technologies in many aspects of health care delivery are interventions being adopted to address these gaps [5-7]. These structural challenges underscore the need for innovative educational solutions that can deliver expert surgical guidance regardless of physical location.

Laparoscopic cholecystectomy (LC) is a technically challenging procedure that residents become familiar with early on under supervision. Potential complications can have serious and hazardous consequences for the patient during major bile duct injury. Substantial hands-on supervision during the initial phases of the learning curve, with gradual achievement of independence, is expected.

Laparoscopic procedures have a complex learning curve that affects clinical and financial outcomes [5,8]. However, expertise in laparoscopic surgery is not readily available, posing a challenge for resident training, particularly in smaller hospitals with limited surgical case volume. These factors call for optimizing the training period for surgical residents. There is some evidence supporting the cost-effectiveness and safety of ST systems [9].

Despite significant technological advances and growing experience with telecommunication and telementoring in health care, the evidence base for educational outcomes remains limited [10-12]. A systematic review by Erridge et al [13] found that, although telementoring demonstrates feasibility and safety, most studies lack rigorous comparative designs to evaluate skill acquisition. A subsequent systematic review from December 2023 by Fernandes et al [14] examined the educational outcomes of surgical telementoring (ST) during surgery. Using ST as the intervention in a continuous professional development program, the authors used the Moores Outcome Framework to evaluate educational outcomes [15]. They reported a lack of high-quality research, such as randomized controlled trials (RCTs), to elucidate the causal effect of ST on educational outcomes.

Furthermore, Chepkoech et al [16] reviewed telementoring systems for surgical training in low- and middle-income countries. They called for standardized qualitative and quantitative metrics, embedded within well-defined training frameworks, to assess the long-term effects of ST on surgical competence and to enable reproducibility and cross-study comparisons.

The Laparoscopic Colorectal (Lapco) Training the Trainers (TT) program, developed in the United Kingdom, provides a validated framework for standardized surgical mentoring and communication. The program established structured communication protocols between the mentor (trainer) and mentee (trainee) during Lapco surgery [17,18]. These principles have been adopted internationally, including in the Norwegian adoption (LapcoNor), to ensure consistent, high-quality intraoperative teaching.

Initiated in 2014, LapcoNor was a collaboration between the Norwegian Health Authority (South East) and Lapco International UK to standardize training in Lapco surgery in Norway [19]. The Norwegian program was described in detail in the Norwegian surgical journal, *Kirurgen* [20]. Its standardized communication framework provides an ideal foundation for ST, where a clear, structured dialogue is essential to overcome the physical separation between mentor and trainee. The Lapco TT program, adapted to Norway by the LapcoNor group, was used exclusively to prepare and train the involved mentors prior to participation. LapcoNor principles served as the intraoperative communication framework during resident supervision of surgical procedures.

Multimedia Appendix 1 describes how the LapcoNor group supervised the included telementors and on-site mentors to integrate the communication principles described by Mackenzie et al [17] into the study.

While Lapco principles were used at the micro level to facilitate concise verbal communication and enhance technical competency by addressing surgical challenges, the GROW (goals, reality, options, wrap-up) model was used for surgical coaching [21,22]. Surgical coaching has emerged as an effective method for developing surgical competence and will be implemented using the GROW model. Unlike mentoring, surgical coaching using the GROW model provides a macrostructure for verbal interactions during the telementoring session. It may facilitate the mentee’s ability to make independent decisions, thereby evolving both technical and nontechnical surgical skills. A description of the GROW model of surgical coaching, adapted for telementoring sessions, is provided in Multimedia Appendix 2.

There has been a focus on procedure-specific metrics to structure surgical education and assessment, minimizing subjectivity in the trainee-trainer relationship. van Zwieten et al [23] presented a systematic review of assessment methods in Lapco surgery. They differentiated between procedure-specific and general rating scales for the objective assessment of technical skills, enabling accurate feedback in a training environment.

This study applies Lapco communication principles and standardized coaching using the GROW model in the intervention arm, thereby minimizing communicative bias while evaluating the educational efficacy of the telementoring modality. Using the Global Operative Assessment of Laparoscopic Skills (GOALS) score, the most widely used general rating system for laparoscopic procedures, the study enables comparison with existing and future literature. The GOALS score, including its parameters and scoring systems, is shown in Figure 1.

Given the increasing reliance on remote surgical education following the COVID-19 pandemic, there is a need for RCTs to assess ST as an intervention, enabling the acquisition of technical and nontechnical surgical skills to improve individual surgeons’ performance and patient outcomes. An RCT of this caliber will inherently pose strategic and practical challenges that require resources, which might be wasted due to poor study design [24]. Pilot trials are recommended as an essential initial step in assessing the feasibility of a full-scale RCT [25].

ST may offer several advantages over traditional hands-on mentoring: (1) the telementor shares the same visual perspective as the operating resident without competing for the operative field; (2) the structured communication required in telementoring may enhance deliberate feedback; (3) the combination of real-time guidance with systematic postoperative coaching using the GROW model may reinforce learning more effectively than traditional, unstructured mentoring; and (4) the telementor can provide undivided attention to teaching without the distraction of potentially needing to take over the procedure.

This pilot RCT aims to provide foundational data for a future full-scale trial. The study aims to evaluate whether real-time ST, combined with structured postoperative coaching, is superior to traditional on-site mentoring for developing surgical skills among surgical residents. Our primary hypothesis is that residents receiving telementoring will show a 3- to 5-point improvement in GOALS scores compared with the control group.

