### Intervention Group (Telementoring)

The telementoring protocol comprises 3 main phases: preprocedural setup and coaching, intraoperative telementoring, and postoperative coaching.

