#### Preprocedure Setup and Coaching

Before commencing the surgical procedure, a standardized setup phase of approximately 10 to 15 minutes is implemented. Key steps to ensure operational readiness include the following: the resident confirms connectivity to the telementoring system with the remote mentor; a bilateral communication check of the audio headset is performed, and the video feeds from both the laparoscopic and external OR cameras are verified by the telementor. This phase concludes with a brief preoperative discussion to review the surgical plan and anticipate potential challenges.

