#### Postoperative Coaching (10-15 Minutes Within 1 Hour of Procedure Completion):

A structured coaching session is conducted postoperatively, within 1 hour of procedure completion, and lasts approximately 10 to 15 minutes. This session uses the GROW model and is conducted via a videoconferencing platform.

The process begins with the resident completing a self-assessment of their performance, focusing on their initial goals and the actual surgical outcomes (goals and reality). Subsequently, the mentor provides constructive feedback, referencing specific procedural moments observed during the operation. The session concludes with the joint identification of specific action points for improvement (options and wrap-up). Finally, the key learning points generated during the session are formally documented for future reference and to support the continuity of training.

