#### Postoperative Feedback

Postoperative feedback in this group consists of a standard informal debriefing, conducted solely at the mentor’s discretion. This approach is defined by the absence of mandated structure, specific timing requirements, or formal documentation requirements. This methodology represents the current standard practice in many surgical training environments.

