## Discussion

### Principal Findings and Interpretation

We acknowledge that telementoring is often positioned as an alternative when on-site expertise is unavailable, and the intuitive assumption is that physical presence should be superior. However, our superiority hypothesis is based on several theoretical considerations.

First, telementoring may enhance the quality of verbal instruction. When the mentor cannot physically intervene, communication must be more precise and explicit, potentially improving the teaching dialog. The structured communication required by telementoring (stop-identify-explain-instruct-check-judge) enforces a pedagogical framework that may be applied less rigorously when mentors can simply take over the instruments.

Second, the mandatory structured postoperative coaching in the telementoring arm (using the GROW model) represents an educational enhancement not typically provided in traditional training. This combination of real-time guidance and systematic reflection may amplify learning beyond that achieved through informal feedback.

Third, the telementor maintains the identical visual perspective as the operating resident without competing for the operative field or camera control, potentially allowing for more focused observational teaching.

We acknowledge, however, that these are theoretical advantages that may not materialize in practice. The pilot study will test whether any educational benefit exists and, equally importantly, will provide data to refine or reject this hypothesis before investing in a larger definitive trial. If the pilot demonstrates no advantage—or disadvantage—for telementoring compared to on-site mentoring, this finding would itself be valuable, suggesting that telementoring can serve as an acceptable equivalent (noninferior) alternative when on-site expertise is unavailable.

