### Future Directions

The results of this pilot study will directly inform the design of a definitive multicenter RCT. Specific aspects that may require modification include recruitment strategies, randomization procedures, outcome timing, and telementoring protocols. If substantial technical or logistical barriers are identified, alternative technological solutions will be explored before the definitive trial.

Beyond the immediate next steps, successful demonstration of telementoring efficacy could enable expansion to other laparoscopic procedures, support the development of national telementoring networks for rural surgical training, and inform educational policy for surgical residency programs in geographically challenging regions.

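### Structured coaching and structured communication come only with the intervention arm, so neither a GOALS difference nor a null result can be attributed to telementoring itself, as the Discussion does

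*Protocol article*

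**What the plan says.** **The aim is a package.** The Introduction asks "whether real-time ST, combined with structured postoperative coaching, is superior to traditional on-site mentoring". The next sentence gives the hypothesis in shorter form: "Our primary hypothesis is that residents receiving telementoring will show a 3- to 5-point improvement in GOALS scores compared with the control group".

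**Intervention arm.** Under Intervention Group (Telementoring): "The telementoring protocol comprises 3 main phases: preprocedural setup and coaching, intraoperative telementoring, and postoperative coaching". Intraoperative Telementoring adds the six-step Lapco communication sequence. For the coaching: "A structured coaching session is conducted postoperatively, within 1 hour of procedure completion, and lasts approximately 10 to 15 minutes". Table 2 calls this session mandatory, but gives it 15 to 20 minutes.

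**Control arm.** Technical Setup of the Telementoring System says that neither Lapco principles nor the GROW model is used in guiding control residents at any stage. Interventions and Intraoperative Mentoring describe unstructured teaching at the mentor's discretion. Under Postoperative Feedback: "Postoperative feedback in this group consists of a standard informal debriefing, conducted solely at the mentor’s discretion".

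**What is to be concluded.** Principal Findings and Interpretation gives the coaching as its own reason to expect superiority, since it "represents an educational enhancement not typically provided in traditional training". The same section would take a finding of no advantage as a sign that telementoring is a noninferior substitute. Comparison to Prior Work says that training all mentors alike lets the study separate out the effect of the modality. The Introduction speaks of evaluating the educational efficacy of that modality. Future Directions says that "successful demonstration of telementoring efficacy could enable expansion to other laparoscopic procedures". The Limitations section does not mention that several components were changed together.

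**The concern.** If coaching, structured communication and remote mentoring always arrive together, the GOALS contrast estimates their joint effect. The article itself expects coaching to work, and nothing in the coaching content (self-assessment, feedback, action points) needs a remote mentor. A positive result could therefore come partly or wholly from elements that an on-site mentor could deliver, yet be cited in support of telementoring networks. A null result could hide a loss from remote mentoring that coaching made good, yet be cited as evidence that remote mentoring is as good as on-site mentoring. A hospital adopting telementoring without the coaching would be relying on evidence that does not apply to it.

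**Working it through.** **1. The plan's own figure.** The concern disputes no number in Sample Size. The inputs there are SD 2.5, a difference of 3 to 5 points, power 0.8, significance level .05 and 20% dropout, giving 12 per group. With n = 2(z_α + z_β)² SD² / δ² and δ = 3:

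- one-sided: 2 × (1.645 + 0.842)² × 6.25 / 9 = 8.6, so 9; 9 / 0.8 = 11.25, so 12;
- two-sided: 2 × (1.960 + 0.842)² × 6.25 / 9 = 10.9, so 11; 11 / 0.8 = 13.75, so 14.

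The stated 12 is reproduced at the 3-point end (exactly if one-sided, within 2 if two-sided). The 3 to 5 points can only be the effect of the whole package.

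**2. Components by arm.**

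| Component | Intervention | Control |
|---|---|---|
| Mentor | Remote | On site, scrubbed |
| Structured intraoperative communication | Yes (Intraoperative Telementoring) | No (Technical Setup; Intraoperative Mentoring) |
| Structured postoperative coaching | Mandatory, every procedure | Not given; informal debrief at the mentor's discretion |

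All three rows change with allocation and with nothing else. The regression in Statistical Analysis adjusts for experience, first-procedure GOALS, residency year, site and complexity. None of these can separate components that coincide with arm.

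**3. Size of the coaching difference.** The text gives 10 to 15 minutes per session and Table 2 gives 15 to 20. Over 5 procedures that is 50 to 75 or 75 to 100 minutes per resident, so 50 to 100 across both ranges. Control has no mandated minutes.

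**4. What a package effect leaves for the modality.** The documents give no split, so the share below is an assumption, as is additivity. It is the part of the package effect due to coaching and structured communication. The last column is the two-sided n per group (80% power, SD 2.5, 20% dropout) that a trial of remote mentoring alone would need.

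| Package effect | Assumed share of coaching and structure | Left for remote mentoring | n per group |
|---|---|---|---|
| 3 | 0% | 3.00 | 14 |
| 3 | 25% | 2.25 | 25 |
| 3 | 50% | 1.50 | 55 |
| 3 | 75% | 0.75 | 219 |
| 5 | 0% | 5.00 | 5 |
| 5 | 25% | 3.75 | 9 |
| 5 | 50% | 2.50 | 20 |
| 5 | 75% | 1.25 | 79 |

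At a share of 100%, remote mentoring contributes nothing while the package still shows its full 3 or 5 points. Every row within a package effect gives the same expected arm difference, so the two-arm data cannot tell the rows apart at any n.

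**5. The null case.** Under the same additive assumption, package effect = modality effect + effect of coaching and structure. If the package effect is 0 and coaching with structure is worth +c points, the modality effect is −c. For c = 1 to 3, a null result would conceal a loss of 1 to 3 points.

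**6. The stated basis for isolation.** Comparison to Prior Work rests the claim on both mentor groups having the same communication training. That does nothing about the coaching session. It also conflicts with other sections. Technical Setup, Interventions and Intraoperative Mentoring withhold the structured framework from controls. The Mentors eligibility criteria and Strengths say that both arms follow standardized communication, and The Surgical Procedure says that all residents were instructed in Lapco and GROW.

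**The case against.** The strongest reply is that this is shorthand and a legitimate design. The sentence just before the hypothesis names the combination, as do the Abstract's objective and the opening of Anticipated Outcomes. The Abstract's methods and Sample Size state the hypothesis for the intervention group, and the telementoring protocol is defined as having three phases that include coaching. Comparing a package with usual practice is sound, and the article discloses that coaching may contribute.

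Most of this stands, and it rules out several stronger readings:

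- A reader might infer that the hypothesis deliberately drops coaching. In context it is more naturally an arm label.
- A reader might infer that the pilot effect size would size the wrong trial. The Abstract has the future trial test the same package, so a package estimate is the right input.
- A reader might infer that structured preoperative coaching is also confined to one arm. Despite its heading, that phase is mainly connection, audio and video checks, and then: "This phase concludes with a brief preoperative discussion to review the surgical plan and anticipate potential challenges". No GROW structure is stated for it, and Technical Setup implies that control mentors also give some preoperative guidance.
- A reader might assume a coaching effect and present the chance of a significant result as a false-positive rate. For the package hypothesis, that result is a correct rejection.

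Future Directions is also conditional in tone. But shorthand cannot explain a statement that the design separates out the modality, nor a reading of a null result as noninferiority of telementoring.

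**Conclusion.** The point holds as one of attribution. The randomized comparison is valid for telementoring with structured communication and postoperative coaching against usual on-site teaching with discretionary feedback. It supports no statement, positive or null, about telementoring alone, and the article makes such statements in the Introduction, Principal Findings and Interpretation, Comparison to Prior Work and Future Directions without listing the limit. The documented difference is 50 to 100 mandated coaching minutes per resident against none, plus the communication framework if the control-arm descriptions are taken at face value. How a GOALS difference would divide between components is unknown, and the split in the working is illustrative only. The stated 12 per group is not put in question by this point.

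**What to change.** - Delete from Comparison to Prior Work the claim that the design isolates the modality.
- In the Introduction (the efficacy statement and the hypothesis), Sample Size, Principal Findings and Interpretation, Anticipated Outcomes and Future Directions, name the contrast as telementoring with structured communication and postoperative coaching versus usual on-site teaching with discretionary feedback.
- In Principal Findings and Interpretation, remove the inference that a null result shows telementoring to be noninferior.
- In Limitations, state that neither a positive nor a null result can be attributed to telementoring alone, and that the pilot effect size applies only to the package.
- Reconcile Technical Setup, Interventions and Intraoperative Mentoring (no structured framework in control) with the Mentors criteria, The Surgical Procedure, Comparison to Prior Work and Strengths (both arms use it or are taught it). The package wording should follow the outcome. Reconcile also the two coaching durations.

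Recording feedback minutes in both arms is optional description and would not restore attribution, because coaching would still coincide with arm. If attribution to the modality is wanted, the definitive trial would need the same coaching in both arms, or a factorial or third-arm design.

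The cost is text only, with no change to sample size or conduct, and analysis is not due until November 2026. The downside is a narrower claim.
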